### **2.1 Objectives**

The primary objective of this study is to determine, in a multicentre, randomized controlled trial, whether the use of the PediAppRREST app is associated with a reduction of deviations from international guidelines, in the management of a simulated PCA scenario, compared with the use of the PALS pocket reference card or with the use of no cognitive aid.

The secondary objectives are to further evaluate the usability of the PediAppRREST app and its impact on team members' workload, CPR quality, time to performance of critical resuscitation interventions, and overall team performance.

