### 3.4 Outcomes

#### 3.4.1 Primary outcome

The primary outcome of the study is the number of deviations from the PALS guidelines made by the teams during the management of a standardized simulated scenario of non-shockable PCA.

Deviations from PALS guideline recommendations are defined as delays and errors according to a novel checklist we derived from the previously published checklist by Wolfe et al[20], denominated c-DEV, by integrating it with evidence-based guidelines,[6-8,11] previously reported scoring tools,[40-43] and checklists.[37,44,45] We named our new modified checklist c-DEV15plus. It includes 15 items, which represent correct critical actions for paediatric resuscitation (Table 1).

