Each item of the c-DEV15plus is scored either as 0, when the action is performed correctly and timely, as described in the item, or as 1, when the action is not undertaken, undertaken incorrectly, or with wrong timing and, in the event of drug administration, when the dose, duration or route of administration is wrong. The sum of the points attributed to the items represents the c-DEV15plus total score, hence ranging from 0 to 15, with higher scores corresponding to a higher number of deviations from the guidelines. Outcome assessors will score the scenarios through the c-DEV15plus tool using the data registered and coded by the video reviewers.

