### 3.4.2 Secondary outcomes

The following secondary outcome measures will be collected:

- *Performance and time to accomplish critical resuscitation interventions* recommended by PALS guidelines.[6-11,20] The interventions evaluated will be: (i) cardiac arrest recognition (pulselessness); (ii) start of chest compressions; (iii) start of ventilation; (iv) use of a CPR board or a rigid surface underneath the manikin; (v) call for emergency team help; (vi) start of EKG monitor; (vi) first epinephrine administration; (vii) second epinephrine administration; and (viii) treatment of reversible causes of CA. Performance and time to accomplish critical interventions (in seconds) during resuscitation will be assessed and recorded by video reviewers in the study CRFs and will be analysed both as time from the beginning of the scenario and as time from the recognition of pulselessness.
- *Usability of the app*. To assess the PediAppRREST app usability, the team leaders of the intervention group will be administered one validated questionnaire, the System Usability Scale (SUS).[46,47] Further, the team leader will be asked to complete a questionnaire with open-ended questions.
- *Team leaders' workload* measured by the validated, multidimensional NASA-Task Load Index (NASA-TLX).[48,49] This tool includes six subscale scores that represent independent clusters of variables and different domains of the perceived workload: Mental, Physical, and Temporal Demands, Frustration, Effort, and Performance.
- *CPR quality* measured by the Skill Reporter (Laerdal TM), the internal software of the manikin. CPR quality is defined as: i) proportion of chest compressions with depth 50-60 mm; ii) chest compression fraction (the percentage of time during CA with chest compressions), iii) mean chest compression depth; and iv) mean chest compression rate, according to AHA standards.[7,50]

- Team *resuscitation performance* as evaluated with the Clinical Performance Tool (CPT).[40,41] The CPT is a validated scoring system designed based on PALS algorithms, through which sequence, timing, and quality of specific actions, during different simulated scenarios, can be assessed. The CPT section for the asystole will be used to evaluate teams' performance.

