After the scenario, all participants complete a demographic survey reporting their sex, age, year and type of residency program, experience in simulation and resuscitation, and time from PALS/P-BLS/BLS/ALS/ACLS certification. In addition, all the team leaders complete the NASA-TLX and the team leaders in the intervention arm also evaluate the app usability, by completing the SUS. Subsequently, all participants participate in a 15-minute debriefing during which they receive feedback about their performance, and the teams in the intervention arm are able to provide feedback about the app. During this phase, the debriefer reports the feedback received on the app in a specific CRF.

The videos of the scenarios will be evaluated by two independent, and previously trained, reviewers expert in paediatric emergency medicine and simulation. Training of the reviewers, on

RCT-unrelated PCA simulation videos, will be conducted by the principal investigator (FC), until the reviewers will reach at least 80% inter-rater agreement with the principal investigator. No more than two weeks will lapse between the training and the assessment of the RCT videos. The reviewers will use a standardized data collection form where actions performed by the team and time to performance will be assessed and recorded. Disagreements between reviewers will be resolved by consensus with a third independent reviewer, expert in paediatric emergency medicine and simulation. Inter-rater reliability between reviewers will be monitored and reported. Data pertaining the CPR quality from the manikin software will be extracted and recorded on a specific CRF. The scores on the c-DEV15plus, and all the secondary outcomes will be calculated by outcome assessors based on the data coded and reported by the video reviewers on the CRFs.

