### **3.8.2 Data analysis plan**

The results will be summarized for each study group with counts and percentages for categorical variables, mean and standard deviation (SD) or median and interquartile range for quantitative variables, as appropriate. The normality of the quantitative variables will be checked with the Shaphiro-Wilk test.

The c-DEV15plus scale, the performance and time to accomplish specific resuscitation interventions, NASA-TLX, CPT and cardiopulmonary resuscitation metrics will be compared between groups with one-way ANOVA model, followed by the Tukey-Kramer multiple comparisons adjustment procedure in case of statistical significance.

The outcomes will also be analysed with a linear mixed model considering the team as a cluster to evaluate the influence of participants' characteristics on the outcome. To take into account the correlation of the observations within a team, we will specify an undetermined correlation matrix. In case of a not normal distribution of the model residuals, we will proceed with a transformation in order to normalize the distribution.

Both intention-to-treat and per-protocol analyses will be performed.

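### The supplementary mixed model (Protocol 3.8.2) rests on a within-team correlation that the data cannot identify, because every outcome has one value per team

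*Protocol*

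**What the plan says.** Section 3.8.2 makes the main comparison of the three arms by one-way ANOVA, followed by Tukey-Kramer. It then adds a second analysis: the outcomes will also be "analysed with a linear mixed model considering the team as a cluster", so as to assess how participants' characteristics influence them. For the dependence between observations in the same team, "we will specify an undetermined correlation matrix". I read that as an unstructured matrix.

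The outcome sections define the unit of observation:

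- **c-DEV15plus (primary, 3.4.1):** "the number of deviations from the PALS guidelines made by the teams". "The sum of the points attributed to the items represents the c-DEV15plus total score", so each scenario yields one number from 0 to 15.
- **CPT (3.4.2):** "The CPT section for the asystole will be used to evaluate teams' performance".
- **Times to intervention (3.4.2, 3.6):** coded from video as actions of the team.
- **CPR quality (3.4.2):** taken from the manikin's software. No attribution to individual members is described.
- **NASA-TLX and SUS (3.6):** "all the team leaders complete the NASA-TLX and the team leaders in the intervention arm also evaluate the app usability".

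Objective 2.1, however, refers to the app and "its impact on team members' workload, CPR quality", which suggests that workload is measured on all members.

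**The concern.** A mixed model clustered by team, with its own within-team correlation, needs at least two observations of the same outcome in a team. The three residents each supply covariates through the demographic survey (3.6), but none supplies an outcome of his or her own, apart from the leader's questionnaires. The correlation that the model is meant to handle therefore has no data behind it.

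The protocol does not leave this open for a later document. It names the model, the cluster and the correlation structure, and that combination does not fit its own data collection. At stake is the participant-characteristics analysis. Followed literally, it contains a parameter that cannot be estimated. It also invites a layout of three rows per team, in which one team score would appear three times.

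**Working it through.** **Inputs.** Section 3.8.1: 29 teams per arm raised by 20% gives 29 × 1.2 = 34.8, rounded to 35; 35 × 3 = 105 teams; 105 × 3 = 315 residents. The assumed within-group SD is 2.20. Section 3.3: teams are randomised 1:1:1, and their formation is stratified by site and specialty, which I read as making both common to a whole team. The protocol gives no figure for the mixed model, so there is none to reproduce.

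**Step 1: observations per team.** From the list above, each outcome has one value per team. There are several intervention times and six NASA-TLX subscales, but these are different outcomes, not repeated measurements of one outcome on different members.

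**Step 2: one row per team.** Let σ_b² be the between-team variance and σ_e² the residual variance. Each score has variance σ_b² + σ_e², and different teams are independent. With T = 105 teams and three arm means, the REML kernel is

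−½(T − 3) log(σ_b² + σ_e²) − ½ RSS/(σ_b² + σ_e²),

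which depends on the sum only. In a simulated data set with total variance 3.967, the kernel was −121.279 for σ_b² = 0, 1, 2 and 3.5 alike. The split, and hence the within-team correlation, cannot be estimated. The fixed effects can be, and they are those of ordinary team-level regression.

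**Step 3: three rows per team, team still declared as cluster.** The copies are identical, so the within-team correlation is exactly 1 and a 3 × 3 unstructured matrix is singular. A random-intercept REML fit to copied scores was run 200 times with no true effects:

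- Residual variance collapsed to zero in 200 of 200 fits.
- The arm null was rejected in 70 of 200 (35%).
- An individual-level covariate was rejected in 0 of 200.

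Generalised least squares with the within-team correlation fixed at 0.9 to 0.999 and the correct total variance rejected the arm null in 4.8% to 5.7% of runs. The 35% therefore comes from the degenerate fit, not from clustering as such.

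**Step 4: three rows per team, copies treated as independent.** This is an assumption; the protocol does not state it. Copying multiplies the between- and within-arm sums of squares by 3, and the error df go from 105 − 3 = 102 to 315 − 3 = 312. The F statistic is therefore multiplied by 312/102 = 3.059. The true false-positive rate of a nominal 5% test with q df is P[F(q, 102) > F_crit(q, 312)/3.059].

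| Term | F_crit | F_crit/3.059 | False-positive rate |
|---|---|---|---|
| Team-level, 1 df | 3.871 | 1.266 | 26.3% |
| Arm, 2 df | 3.025 | 0.989 | 37.6% |

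Simulation (3,000 runs) gave 27.8% and 37.8%. In the same simulation, the arm test with one row per team gave 4.7%. A characteristic varying independently within teams gave 5.3%, and one with an assumed within-team correlation of 0.3 gave 13.1%.

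**The case against.** The strongest reply is that this is a wording slip in a supplementary analysis. The ANOVA on one score per team carries the arm comparison, and the sample size counts scenarios, one per team. With one row per team a fixed-effects fit is still available, so the surplus variance parameter does no numerical harm. Row layout and covariate lists are commonly left to an analysis plan. Most of this stands and sets the severity. It does not rescue the sentence: the model, cluster and correlation matrix are fixed in the protocol, and an analysis plan that followed them would inherit the mismatch.

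A reader might infer two stronger things.

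- **That the analysis cannot be fitted at all.** This goes too far. What cannot be estimated is the team variance and the within-team correlation. Effects of arm, leader characteristics and team summaries remain estimable by team-level regression.
- **That the plan carries a false-positive rate of 26% to 38%.** The document does not support this. Nothing in it says that team scores will be copied to members, and the sentence is there to account for within-team dependence, not to ignore it. The figures also apply to terms shared by a whole team, whereas the stated purpose is participants' characteristics. Those that vary independently within a team stay near 5% even under that layout.

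The workload wording in 2.1 is a separate inconsistency and does not support the modelling point. Sections 3.4.2 and 3.6 are explicit that leaders are the respondents.

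**Conclusion.** The point holds in this form: the mixed model in 3.8.2 has no within-team replication for any outcome, its correlation matrix is not identifiable, and as written it cannot serve its purpose of assessing participants' characteristics. This rests only on the outcome definitions and on who completes each questionnaire, plus the reading that the manikin yields one set of CPR metrics per scenario.

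The primary ANOVA and the sample size are not affected. The range of about 26% (1 df) to 38% (2-df arm test) is conditional on copied scores being analysed as independent. It is a reason to close off that layout, not a property of the stated plan. Severity: should-fix, because this is an additional analysis.

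**What to change.** Replace the mixed-model sentences in 3.8.2 with a team-level linear model, one row per team (planned N = 105). Regress each outcome on:

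- arm, site and specialty;
- team-leader characteristics, such as year of residency, time since certification and resuscitation experience;
- team summaries of member characteristics, such as the number of PALS-certified members or the mean year of residency.

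Use no team random effect and no within-team correlation matrix, and state that team scores are not to be repeated across members. Arm, site and specialty take 2 + 3 + 2 = 7 df, which with the intercept leaves 105 − 8 = 97 for the remaining terms and error. The particular leader and team covariates are for the investigators to choose. SUS is collected in the app arm only, so its model has no arm term.

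In 2.1, change the workload objective from team members to team leaders, to match 3.4.2 and 3.6. Collecting NASA-TLX from all three members is not needed for this. It would be hard to add now, since 3.5.2 shows the trial already under way and teams already assessed could not supply it.

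The cost is protocol wording only. The survey already collects the covariates, and no new data are required.

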## **3.9 Patient and Public Involvement**

No patient involved.

## **4. ETHICS AND DISSEMINATION**

The design of this study complies with the Declaration of Helsinki ethical principles, Good Clinical Practice standards, and European Union general data protection regulation on scientific research. Participation into the study is on a voluntary basis and bears no academic or professional consequences on the medical residents. A written informed consent to take part into the study is obtained from each participant. The Human Ethics Committee (HEC) of the University Hospital of Padova, coordinating centre of the trial, deemed the trial to be a negligible risk study and approved it through an expedited review process.

The results of the study will be disseminated in peer-reviewed journals, national and international scientific conferences, and medical residency training programs educational sessions. After publication of the study results, the PediAppRREST app will be released exclusively to institutions/health care professionals, upon request.

Any adverse event will be communicated to the principal investigators and recorded in the participant CRF. In the extremely unlikely event of a serious adverse event, the principal investigators will be informed immediately and the HEC will be notified within 24-72 hours of occurrence.

This trial is registered in [clinicaltrials.gov](https://clinicaltrials.gov), ID: NCT04619498 (November 6, 2020).

## **6. FUNDING STATEMENT**

This research has received funding support from internal grants from the University of Padova (BIRD 191291).

## **7. COMPETING INTERESTS STATEMENT**

The authors declare that they have no competing interests.

### *Simulation scenario*

Case scenario: a case of non-shockable paediatric cardiac arrest caused by hypovolemia and hypoglycaemia.

Team: three paediatric residents and one confederate nurse.

Setting: off-site, in a room set reproducing the environment and the equipment of a paediatric emergency department shock room.

Introduction: A 4-year-old child (22 kg weight) is brought to the Emergency Department by his mother; she refers diarrhoea and vomiting in the past 5 days. Today the boy has been lethargic and difficult to wake up; the triage nurse brings him straight to the shock room.

Information about the clinical case is provided to participants through a video where an actress plays the role of a mother who brings her child to the Paediatric Emergency Department.

The following information about the child are conveyed through the video:

- Age: 4 years;
- Weight: 22 Kg;
- Signs/Symptoms: vomiting and diarrhoea for the previous 5 days, minimal fluid intake for the past 2-3 days;
- Allergies: no allergies;
- Medications: no medications;
- Past history: previously healthy child;
- Last meal: more than 48 hours before;
- Events: child has been sleeping for the previous 2 hours, not responding to physical stimulation.

The scenario starts with a pulseless unconscious child who is suffering a cardiac arrest characterised by pulseless electrical activity (PEA) rhythm for 2 minutes, followed by asystole.

Return of spontaneous circulation (ROSC) is achieved if at least two correct doses of epinephrine are administered timely and hypovolemia +/- hypoglycaemia are addressed. The scenario runs for 10 minutes following the end of the introductory video, regardless of the actions performed by the team.
